**10. Analysis**

We will report descriptive sociodemographic and clinical data by randomisation group. We will conduct between group comparisons for categorical and linear data. We will compare the mean MMSE from each group and will use t-tests or Mann-Whitney where appropriate. Statistical modelling will be performed in the form of hierarchical multivariate regression analysis, to account for clustering of patients. Analysis of covariance (ANCOVA) will be used to adjust for baseline differences in outcome variables and multiple linear regression will be used to identify other predictors of MMSE at presentation e.g. gender, age and ethnicity. In the regression analysis we will account for the clustering effect in suitable ways (e.g. random effects models). We plan to perform a primary analysis on complete cases and then develop secondary analyses adjusting for potential missing data using suitable methods (e.g. multiple imputations, and inverse probability weighting). We will apply these as sensitivity analysis and discuss them in conjunction with the main analysis. Missing data is accounted for in the sample size calculations; thus we should be able to observe enough complete cases to preserve the power for the main analysis. For the cost analysis the costs associated with printing and distributing the CHOICE leaflet will be based on market prices. Numbers of GP visits will be taken from MiQUEST29 and numbers of contacts with memory services will be taken from practice records. All contacts will then be costed by applying unit costs from published sources41. We will then calculate and compare the mean cost of delivering the intervention per patient and the use of GP and memory services in each arm.

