**9. Power calculations and statistical methods to be used**

Sample size

Approximately 14% (1 in 7) of people aged >70 have dementia37. The average GP registered patient population is ≈200038, of whom 260 (13%)39 are ≥70 years old. Thus there is a mean of 36-37 patients with dementia per GP of whom 24 would be unknown. An audit of people with dementia presenting to Islington memory services showed a mean MMSE score =19.5 (standard deviation=6.1). A clinically significant difference between experimental and control arms =3 points in MMSE2. To achieve this would require 71 undiagnosed people with dementia in each group (=5% and power=90%). In Islington last year 420 patients were referred from the 38 practices – a mean of 11/practice. Since families in group practices may receive the intervention letter from one GP then consult and be referred by another, cluster randomisation is appropriate and will be used to allocate GP practices to the intervention or control arms. Consequently, we need to inflate the sample based on a projected intracluster correlation of 0.0340. The required sample size in each arm is then 93. This will equate to 8580 people aged over 70 registered with the GPs. If 11 patients are referred per practice, we require approximately nine practices (clusters) in each trial arm. The primary outcome is routinely collected data; but some patients will become too ill or die, or refuse assessment by the clinics. Estimated level of attrition rate=18% (18% loss to follow up in LASER including deaths- a previous dementia study in the community), and therefore we aim to recruit 11 GP practices in each arm. Randomisation will be computerised and stratified by geographical location. The allocation ratio will be 1:1.

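### Section 10 compares the primary outcome with a test that ignores clustering, alongside a model that respects it, and does not say which decides the trial

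*Protocol*

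**What the plan says.** Section 9 of the protocol allocates whole practices, 1:1, stratified by geographical location. It accepts that patients of one practice are correlated: "we need to inflate the sample based on a projected intracluster correlation of 0.0340" (the final 40 is a reference number, so the value is 0.03).

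Section 10 gives the comparison of the primary outcome: "We will compare the mean MMSE from each group and will use t-tests or Mann-Whitney where appropriate". It continues: "Statistical modelling will be performed in the form of hierarchical multivariate regression analysis, to account for clustering of patients". ANCOVA and multiple linear regression follow. A later sentence on allowing for clustering, with random effects as an example, is confined to the regression analysis.

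Section 10 uses the term primary analysis once, for the complete-case data set as opposed to the missing-data analyses. It does not attach the term to any test or model.

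**The concern.** A t-test or Mann-Whitney on individual patients treats them as independent. In a trial that randomises practices they are not, and Section 9 says so by inflating the sample size. The sentence that compares mean MMSE between arms therefore conflicts with the design it serves. A version on practice means would be valid, but none is mentioned, so the patient-level reading is the natural one.

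The section lists several analyses of one outcome without ranking them. An SAP that made the t-test decisive would comply with this wording, and so would one that made the hierarchical model decisive. The first would give a p-value that is too small and an interval that is too narrow. With the choice open, the more favourable result could also be put forward once the data are seen.

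**Working it through.** **Inputs, all from Section 9:** "A clinically significant difference between experimental and control arms =3 points in MMSE2" (the final 2 is a reference number); "mean MMSE score =19.5 (standard deviation=6.1"; 5% level with 90% power, sidedness not stated; ICC 0.03; "If 11 patients are referred per practice, we require approximately nine practices (clusters) in each trial arm"; attrition 18%; 11 practices per arm after attrition.

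**1. Reproduce the plan's sample size.** n per arm = 2(z_α + z_β)² SD²/δ².
- One-sided 5%: 2 × (1.645 + 1.282)² × 6.1²/3² = 70.8, rounded up to 71. This matches "To achieve this would require 71 undiagnosed people with dementia in each group".
- Two-sided 5%: 2 × (1.960 + 1.282)² × 6.1²/3² = 86.9, rounded up to 87. This does not match.
- Design effect = 1 + (11 − 1) × 0.03 = 1.30; 71 × 1.30 = 92.3, rounded up to 93 per arm, as stated.
- 93/11 = 8.5, so 9 practices; 9/(1 − 0.18) = 10.98, so 11 practices, as stated.

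**2. Patients per practice in the analysis.** 11 as planned, or 11 × 0.82 = 9.02, about 9, after attrition. At 9 the design effect is 1 + 8 × 0.03 = 1.24.

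**3. Actual error rate of an unclustered test at nominal 5%.** The test understates the variance of the difference by the design effect (DE). The actual rate is 2[1 − Φ(1.960/√DE)] two-sided, or 1 − Φ(1.645/√DE) one-sided.

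| Patients per practice | DE | Two-sided | One-sided |
| --- | --- | --- | --- |
| 11 | 1.30 | 1.960/1.140 = 1.719 → 8.6% | 1.645/1.140 = 1.443 → 7.5% |
| 9 | 1.24 | 1.960/1.114 = 1.760 → 7.8% | 1.645/1.114 = 1.477 → 7.0% |

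**4. Width of the confidence interval.** Reported width over correct width is 1/√DE: 0.88 at DE 1.30 (12% too narrow) and 0.90 at DE 1.24 (10% too narrow).

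**5. Check by simulation.** Normal data, no treatment effect, ICC 0.03, equal practice sizes, two-sided 5%; 40,000 trials for the t-tests and 6,000 for Mann-Whitney.

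| Practices per arm × patients | Patient t-test | Mann-Whitney | t-test on practice means |
| --- | --- | --- | --- |
| 9 × 11 | 8.7% | 8.8% | 5.2% |
| 11 × 9 | 7.8% | 7.5% | 5.0% |
| 11 × 11 | 8.6% | 8.1% | 4.9% |

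Switching from the t-test to Mann-Whitney does not cure the problem. An analysis at practice level does.

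**6. Sensitivity to figures the protocol does not give (assumptions).** With unequal practice sizes, at an assumed coefficient of variation of 0.4 to 0.65 and 9 or 11 patients per practice, the two-sided rate is 8.4% to 10.2%. With an assumed ICC of 0.01 to 0.05 at 11 per practice, it is 6.2% to 11.0%.

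**The case against.** The strongest reply is that Section 10 already deals with clustering. The hierarchical model comes in the very next sentence, and random effects are mentioned again further on. The t-test follows descriptive reporting and a general statement about group comparisons, so it can be read as an unadjusted first look, with inference left to the model. Nothing calls it primary.

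Much of this stands. A reader might infer that the plan ignores clustering, or that the trial's error rate is simply 8–9%. The document supports neither: the inflation arises only if the unclustered result is treated as decisive. Nor does 8–9% cover all of the protocol's own inputs. After attrition the two-sided figure is 7.8%. On the one-sided reading, the only one that reproduces 71 per arm, it is 7.0–7.5%. Eleven is also a count of referrals, while the outcome is confined to those diagnosed with dementia. Fewer analysed patients per practice would lower the figure further, though unequal practice sizes would raise it.

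A reader might also infer that the hierarchical model is itself anti-conservative with 22 clusters. Section 10 specifies no reference distribution or degrees of freedom, which are commonly left to the SAP, so that criticism has no text to rest on.

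The reply does not remove the ambiguity. Descriptive reporting has its own sentence, the t-test sentence is the one that compares mean MMSE between arms, and the hierarchical model is not tied to the primary hypothesis. Naming an unsuitable test beside a suitable one without ranking them goes beyond leaving detail to an SAP.

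**Conclusion.** The point holds in conditional form. Section 10 offers an unclustered and a clustered comparison of the primary outcome and does not say which decides the trial, although the design and sample size both recognise clustering.

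If the unclustered test decides, a nominal 5% level is in fact about 7–9%, with an interval 10–12% too narrow. This rests on the protocol's ICC of 0.03, 9 to 11 analysed patients per practice and equal practice sizes, and the range covers both readings of the unstated sidedness. If the hierarchical model decides, this inflation does not arise.

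**What to change.** In Section 10:

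- Name one primary analysis of MMSE that respects clustering. A suitable choice is a linear mixed model with treatment as a fixed effect, a random intercept for practice and the geographical stratification factor, with a small-sample degrees-of-freedom correction (such as Kenward-Roger or Satterthwaite) because there are only 22 clusters.
- Delete the patient-level t-test or Mann-Whitney for MMSE, or run it on practice means only.
- Label all other models of MMSE as supportive.

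The change is to wording and needs no new data. The interval becomes wider, but correct, and this is the kind of analysis for which the sample was inflated from 71 to 93.

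The sidedness of the 5% level should be stated consistently with the sample size calculation. That is a separate issue, but it bears on power. With 11 practices of 9 patients per arm, the effective size is 99/1.24 = 79.8 per arm and the standardised difference is 3/(6.1 × √(2/79.8)) = 3.11. On a t distribution with 20 degrees of freedom, power is about 91% one-sided and 84% two-sided, against the planned 90%.

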**1. Aims of the project**

The primary aim of this study is to increase timely diagnosis of dementia through an evidence-based intervention promoting memory service access. We will test in a randomised controlled trial if this intervention increases the number of people with undiagnosed dementia presenting with memory related problems to their GP; the number of patients GPs refer appropriately to memory services; and if this referral is at an earlier stage. We are currently collaborating with the Alzheimer’s Society and their reference groups (including the GP reference group) to redesign the evidence-based CHOICE leaflet1 to ensure usability, acceptability and relevance, and to develop a personal letter from GPs to the “at risk” population to accompany the leaflet.

Research questions

Does sending a leaflet1 on how to overcome barriers to accessing help for dementia to people aged over 70 registered in a general practice, with an accompanying personal letter from the GP, lead to people with dementia presenting earlier to specialist dementia services compared with usual care over 12 months, and if so is it at low cost? We will test the hypotheses that over 12 months people receiving the intervention will present earlier (mean of 3 points higher on MMSE score)2 than those not receiving it and that the costs of the intervention are small.

Primary objective

To enable people with dementia to receive an earlier diagnosis

Secondary objectives

1. To increase the number of people with dementia receiving diagnoses
2. To increase the numbers of people with memory problems presenting to GPs.
3. To calculate the cost-effectiveness of the intervention considering the cost of implementing the CHOICE intervention and the numbers of appropriate and inappropriate referrals to memory services.

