**8. Data collection**

All data will be anonymised and collected for intervention and control practices. Consent will be through cluster guardians32, who will provide consent for collection of this data33.

1. Sociodemographic data about the person with suspected dementia will include gender, age, ethnic status according to census, marital status, education, living situation and location. We will record GP characteristics and practice size.
2. **The primary outcome** is the cognitive score as measured by the Mini Mental State Examination (MMSE)34 of people referred to memory services in the intervention and control groups who receive a diagnosis of dementia. The minimum clinically important difference in MMSE score is three points2 and is the most widely used standard test of cognitive function34. We will collate the baseline MMSE score from the new patients’ presenting to memory clinic (i.e. MMSE scores of new presentations) at 3, 6 and 12 months after sending the letters. We are not collecting follow-up MMSEs. There is a maximum score of 30, with scores of 0-10=severe, 11-20=moderate, and 21-24=mild dementia35.
3. **Secondary outcomes**

- Number of people presenting with a possible diagnosis of dementia will be collected from GPs practices using MiQUEST36 (a Department of Health computer system allowing anonymised data extraction from GP practices). [name] is an expert in using this and is one of the project team. We will collect the number of people presenting to their GP who are and who are not referred on to memory services.
- Numbers of patients referred to memory services from participating intervention and control practices
- The number of memory services appointments offered and people attending for diagnostic assessment,
- The number of people referred who do not have dementia or mild cognitive impairment
- Costs of implementing the intervention, including the costs associated with the CHOICE leaflet (printing, and distribution), GP visits to discuss possible diagnoses of dementia, and use of memory services, and the cost of assessing those with and without dementia
- We will systematically ask clinicians about any inappropriate presentations and patient distress and record these as adverse events.

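### Objective 3 promises cost-effectiveness, but the economic analysis stated in section 10 compares costs and service use by arm and never relates them to an effect

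*Protocol*

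**What the plan says.** The Protocol describes its economic aim in four places.

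- **Section 1, secondary objective 3:** "To calculate the cost-effectiveness of the intervention considering the cost of implementing the CHOICE intervention", together with the numbers of appropriate and inappropriate memory-service referrals.
- **Section 1, research questions:** the economic hypothesis is only "that the costs of the intervention are small".
- **Section 10:** the work is called a cost analysis. It opens with "For the cost analysis the costs associated with printing and distributing the CHOICE leaflet will be based on market prices", takes GP visits and memory-service contacts from records, applies published unit costs, and ends with the plan to "calculate and compare the mean cost of delivering the intervention per patient and the use of GP and memory services in each arm".
- **Figure 2 (timetable):** the same work appears as determining cost benefits.

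Section 8 lists what will be collected. On the effect side it has "Numbers of patients referred to memory services from participating intervention and control practices" and "The number of people referred who do not have dementia or mild cognitive impairment". On the cost side it has leaflet costs, GP visits, "use of memory services, and the cost of assessing those with and without dementia".

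**The concern.** Cost-effectiveness sets a difference in cost against a difference in effect. Section 10 describes the economic work from its inputs to its final output, and that output contains no effect. The referral counts that objective 3 names do not enter it.

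This matters more here than in many trials because the intervention is meant to raise activity. Secondary objectives 1 and 2 seek more diagnoses and more people presenting to GPs. Higher service use, and hence higher cost, in the intervention arm is therefore part of the intended result. A comparison of cost and use cannot by itself separate extra activity that led to dementia being recognised from extra activity spent on people with neither dementia nor mild cognitive impairment. Objective 3 asks for that distinction, and commissioners, who are a planned audience in Figure 2 and section 11, would need it.

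**Working it through.** The protocol states no cost, ratio, threshold or economic effect size, so there is no figure to reproduce. The check sets the objective, the data and the analysis side by side.

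**1. What the objective requires.** For each arm, let C be the mean total cost per eligible registered patient and E the mean effect per eligible registered patient (appropriate referrals, or new dementia diagnoses). Then:

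- cost difference: ΔC = C(intervention) − C(control)
- effect difference: ΔE = E(intervention) − E(control)
- incremental ratio: ΔC / ΔE, with an interval that reflects randomisation by practice.

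**2. What section 10 supplies.**

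| Element | In the section 10 economic analysis? |
|---|---|
| Cost of leaflet and distribution | Yes, at market prices |
| GP and memory-service contacts, with unit costs | Yes |
| Comparison of cost and use by arm | Yes |
| ΔE on appropriate referrals or diagnoses | No |
| Any step joining ΔC to ΔE | No |
| Denominator for the per-patient cost | Not defined |

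The analysis reaches ΔC, or its components, and stops. The same ΔC is compatible with a large ΔE, a small one or none, so ΔC alone does not determine cost-effectiveness. The delivery-cost part of the comparison also carries little information, since control practices send no letters under the trial. The informative part is service use, where a rise is intended.

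**3. What section 8 makes possible.** Costs are collected for implementation, GP visits and memory-service use, with assessment cost split by dementia status. Referrals are counted by arm, as are referred people found to have neither dementia nor mild cognitive impairment. The number diagnosed with dementia can be obtained because the primary outcome is defined on exactly those people. ΔC and ΔE can therefore be formed without new outcome data. One item needs confirming: section 8 records practice size but does not expressly list the count of eligible over-70s in control practices, which a per-eligible-patient denominator needs.

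**4. The labels.** The research question speaks of low cost, objective 3 of cost-effectiveness, and Figure 2 of cost benefits. These are three different targets. The section 10 analysis can address the first; it does not deliver the second as written.

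**The case against.** The strongest reply has four parts.

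- **The hypothesis is answered.** The economic hypothesis actually posed is that costs are small, and section 10 can address that. This is true, but objective 3 is a separate stated objective and goes further.
- **Effects are reported anyway.** MMSE at diagnosis is the primary outcome, referrals and unnecessary referrals are secondary outcomes, and section 10 plans between-group comparisons. A reader would see costs and consequences for both arms. This also stands: the results would not be silent on what the money bought. What is missing is the step that combines them.
- **Economic method is often left to a later plan.** The form of the ratio and the interval method can reasonably wait for a statistical or health-economic plan, which may exist but is not shown. However, the protocol is not silent here. It states a specific analysis that differs from its own objective, and a later author could follow either.
- **The per-patient wording is probably harmless.** A reader might infer that it means per referred patient, a denominator the intervention itself changes. The text does not say so. For a mailed letter and leaflet, the natural reading is per person mailed. The point that stands is only that the denominator should be stated.

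A reader might also try to size the problem by dividing the 8,580 people over 70 in section 9 by the 93 required per arm, giving about 92. The document does not support that. Section 9 does not say whether 8,580 is per arm or for both arms; if both, 8,580/186 ≈ 46. The 93 counts people with dementia before the attrition allowance, not referrals; 11 practices at 11 referrals each give 121, and 8,580/121 ≈ 71. In any case, a ratio of two denominators measures no error in the between-arm comparison.

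**Conclusion.** The mismatch is real and lies within the protocol's own text: objective 3 names cost-effectiveness, while the stated analysis ends at a comparison of cost and service use. Followed as written, the plan does not deliver that objective.

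It would be too strong to infer that the objective cannot be answered. Section 8 lists both the cost and the effect data, so what has to change is the stated analysis or the wording of the objective.

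The size is limited: one secondary objective, no effect on the primary outcome or its validity, and no numerical magnitude that the document can support. The conclusion assumes that cost-effectiveness carries its usual meaning of cost set against effect, and that no unseen plan already supplies the missing step. If one does, section 10 should still be brought into line with it.

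**What to change.** Choose one of two routes.

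**Route A: keep objective 3 and complete section 10.**

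- Define total cost as letters and leaflets, GP visits, and memory-service assessments of people with and without dementia.
- Take the between-arm difference in total cost per eligible registered patient, and set it against the difference in appropriate referrals, or in new dementia diagnoses, per eligible registered patient. Name one of these as the effect measure and define an appropriate referral.
- Report the incremental cost per additional appropriate referral or diagnosis, and show the difference in inappropriate referrals alongside it. A separate cost per additional inappropriate referral is not needed, since it has no clear meaning for a decision.
- Use uncertainty intervals that allow for clustering by practice. The exact method can be left to the analysis plan, but resampling practices within arm and stratum would be fragile with so few practices.

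**Route B: reword objective 3 as a comparison of costs and service use**, which section 10 already describes.

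Under either route, state that per patient means per eligible registered patient, confirm that this count will be taken in both arms, and use one consistent term in the research question, objective 3 and Figure 2.

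Route A costs modest extra analysis, and the ratio may be imprecise with about 11 practices per arm. Route B costs only wording, but gives up the cost-effectiveness claim.
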